**Methods:**

This is a stratified, cluster randomized controlled trial conducted in Guangdong Province, China. Schools will be stratified by regional economic development level and randomly assigned to either an intervention or control group. The intervention group will receive annual dental examinations, biannual FV applications, and oral health education. The control group will receive standard annual examinations and comparable oral health education. Participants will be students aged 5 to 22 years enrolled in selected special education schools. Baseline assessments and 12-month follow-ups will include oral examinations and questionnaires assessing oral health knowledge, attitudes, and behaviors. The primary outcome is the difference in caries prevalence between the intervention and control groups at follow-up. Secondary outcomes include changes in oral hygiene behaviors and caregiver knowledge. Data will be analyzed using multivariable regression models adjusting for potential confounders and clustering effects.

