### Sample Size

The primary outcome of this study is the prevalence of dental caries at 12 months. On the basis of previous literature in comparable populations, the prevalence of caries among students in special education schools without intervention is estimated at 60% [5,14]. A reduction to 40% in the intervention group is considered clinically and politically meaningful [9,15]. Using a 2-sided α of .05 and a power of 90% (β=.10), the required sample size per group for an individually randomized trial is estimated using the formula:

$$n=\frac{{\left(z_{\alpha /2}+Z_{\beta }\right)}^{2}\times \left(p_{1}(1-p_{1})+p_{2}(1-p_{2})\right)}{{\left(p_{1}-p_{2}\right)}^{2}}$$

where *z*_*α*/2_ is 1.96, *Z*_*β*_ is 1.28, *p*_1_ is 0.60, and *p*_2_ is 0.40. Substituting these values gives a sample size of approximately 126 per group under individual randomization. Additionally, this study uses a stratified cluster RCT design, which requires adjustment for clustering using the design effect. The design effect was calculated as 1+(m–1)×*ρ* where *m*=150 (average cluster size, ie, school size), *ρ* is 0.02 (intracluster correlation coefficient). The resulting design effect was calculated as 3.98, yielding an adjusted sample size of 501 students per group. Allowing for an anticipated 10% dropout rate, the final required sample size is 557 students per group, totaling 1114 participants across all clusters. On the basis of the final required sample size of 557 students per group and an average cluster size of 150 students per school, the required number of clusters was calculated as 557/150=3.71 per group. Therefore, at least 4 schools per group, corresponding to a minimum of 8 clusters in total, are required.

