### Study Outcomes

The primary outcome of this study is the prevalence of dental caries among students at 12 months following the intervention. Dental caries will be assessed through clinical oral examinations using the decayed, missing, and filled teeth index (DMFT) for permanent and primary dentition, respectively. These examinations will be conducted in accordance with the national standardized child oral health survey protocol used in China. Briefly, trained and calibrated dental professionals will perform tooth-level examinations using disposable dental mirrors and probes under natural or portable lighting. Dental status for both primary and permanent teeth, including caries experience and related conditions, will be recorded. Examinations will take place in a designated room with adequate lighting [21]. Children will be assessed while seated [22], and wheelchair users will remain in their own wheelchairs. Two familiar teachers or school support staff will attend to assist with communication and comfort [23]. A trained dentist will conduct the examination, and a trained nurse will record the number of decayed, missing due to caries, and filled teeth per child. The blank recording form is provided in Figure 3. To minimize measurement bias, examiners conducting the follow-up assessments will be blinded to the school allocation status.

Secondary outcomes include (1) oral hygiene status (eg, presence of plaque and gingivitis), assessed using gingival health indicators and plaque indices; (2) changes in oral health–related knowledge, attitudes, and practices (KAP) among students, parents, and teachers, measured using a structured questionnaire adapted from the Third National Oral Health Survey [24].

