### Statistical Analysis

All data will be entered into a centralized electronic data capture system with built-in logic checks to ensure completeness and internal consistency. Statistical analyses will be conducted using Stata (version 18.0; StataCorp LLC). Descriptive statistics will first be generated to summarize baseline characteristics of participants in both intervention and control groups, including means, SDs, proportions, and frequency distributions.

Comparative analyses between groups will be conducted on an intention-to-treat basis. Participants will be analyzed according to their randomized group, regardless of receipt of FV. For descriptive and unadjusted comparisons between groups, chi-square tests will be used for categorical outcomes (eg, caries prevalence). For continuous variables, independent-samples *t* tests will be used for normally distributed data, and nonparametric tests (eg, Mann-Whitney *U* test) will be applied for skewed distributions. Paired comparisons (eg, baseline vs 12-month follow-up) within groups will use paired *t* tests or Wilcoxon signed-rank tests as appropriate.

To evaluate the effectiveness of the intervention while accounting for potential confounders and cluster randomization in the primary analysis, mixed-effects logistic regression will be used for binary outcomes, such as caries presence, and mixed-effects linear regression for continuous outcomes, such as the number of decayed teeth [27]. Models will adjust for relevant covariates, including age, sex, socioeconomic status, and baseline oral health status. Multiple imputation with chained equations will be applied to handle missing covariate data. Cluster effects will be accounted for using robust SEs or multilevel modeling, as appropriate. Effect estimates will be presented as adjusted odds ratios or mean differences with 95% CIs. All hypothesis testing will be 2-sided, with a significance level set at *P*<.05. Sensitivity analyses, including subgroup analyses by economic region, will be conducted to assess the robustness of the findings.

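### The trial names and is sized on a difference in caries prevalence, but its stated effect measure is an adjusted odds ratio, so the difference has no cluster-appropriate estimate or interval

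*Protocol article*

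**What the plan says.** Four places in the protocol article bear on this point.

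- **Abstract, Methods paragraph:** "The primary outcome is the difference in caries prevalence between the intervention and control groups at follow-up".
- **Study Outcomes:** "The primary outcome of this study is the prevalence of dental caries among students at 12 months following the intervention". This gives the variable and the time point but no contrast between arms.
- **Sample Size:** control prevalence is put at 60%, and "A reduction to 40% in the intervention group is considered clinically and politically meaningful". The formula has the squared difference of the two proportions in its denominator.
- **Statistical Analysis:** the primary analysis of a binary outcome is mixed-effects logistic regression, adjusted for age, sex, socioeconomic status and baseline oral health. Clustering is handled by a multilevel model or by robust standard errors. On the effect measure: "Effect estimates will be presented as adjusted odds ratios or mean differences with 95% CIs". The mean differences go with the linear model for continuous outcomes. The same section plans descriptive summaries and an unadjusted chi-square comparison, with caries prevalence as its example. No prevalence difference, prevalence ratio or standardisation is mentioned.

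**The concern.** The outcome and the sample size are on the scale of a difference in proportions, while the effect measure is on the odds scale. For a rare outcome this would matter little to a reader, because the odds ratio would lie close to the prevalence ratio. Here the planned prevalences are 40% and 60%, and the two measures are far apart.

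The adjusted odds ratio is also conditional on the covariates in the model. Odds ratios are non-collapsible, so adding a strong predictor changes the value even when the arms are balanced on it and the effect on prevalence is the same.

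At stake is whether the main result can be set beside the 20-point reduction that the plan calls meaningful. As written, it cannot be compared directly. The one comparison that is on the prevalence scale would not carry a valid interval.

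**Working it through.** **1. The plan's own figures.** Inputs from Sample Size: 0.60 and 0.40, two-sided 5% level (1.96), 90% power (1.28), cluster size 150, intracluster correlation 0.02, dropout 10%.

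- Individual randomisation: (1.96 + 1.28)² × (0.6×0.4 + 0.4×0.6) / 0.2² = 125.97, stated as 126.
- Design effect: 1 + 149 × 0.02 = 3.98. Then 126 × 3.98 = 501.5, stated as 501.
- Dropout: 501 / 0.90 = 556.7, stated as 557 per group and 1114 in total.

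All of these reproduce. The calculation is built on a difference in proportions.

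**2. Three measures at the planning rates.**

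| Measure | Formula | Value |
|---|---|---|
| Prevalence difference | 0.40 - 0.60 | -20 points |
| Prevalence ratio | 0.40 / 0.60 | 0.667 |
| Odds ratio | (0.40/0.60) / (0.60/0.40) | 0.444 |

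If 0.444 were taken for a prevalence ratio, 60% would seem to fall to 0.60 × 0.444 = 26.7% rather than to 40%.

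**3. The odds ratio does not fix the difference.** Hold the odds ratio at 0.444 and vary control prevalence:

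| Control | Intervention | Difference |
|---|---|---|
| 30% | 16% | -14 points |
| 60% | 40% | -20 points |
| 80% | 64% | -16 points |
| 90% | 80% | -10 points |

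**4. Conditioning on school and covariates.** Keep the marginal prevalences at 60% and 40%, and find the conditional odds ratio that produces them by integrating over a normal term in the logistic model.

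- *School intercept.* With intracluster correlation 0.02, 0.05 and 0.10 (treated as latent-scale values, an assumption), the conditional odds ratio is 0.439, 0.430 and 0.415. At the planned 0.02 the shift is negligible.
- *Prognostic covariates.* With the standard deviation of the covariate part of the linear predictor assumed to be 1, 2 or 3, it is 0.375, 0.263 or 0.172. The documents do not give this standard deviation, so these values show a direction and a range and are not a forecast.

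**5. The crude comparison.** A chi-square test treats students as independent. With the plan's design effect of 3.98, a standard error from that calculation is too small by a factor of √3.98 ≈ 2.0. With about 1100 students in 12 schools (Results), the mean is about 92 per school. The design effect is then 1 + 91 × 0.02 = 2.82 and the factor √2.82 ≈ 1.7. Either way, an interval for the difference built on that comparison would be far too narrow.

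**The case against.** A good deal can be said for the plan.

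- The odds ratio is a legitimate measure, and the logistic model tests the hypothesis of no effect on caries presence. Both points stand. A reader might infer that the plan exaggerates the effect or fails to answer its question. The document does not support this: it nowhere reads an odds ratio as a relative reduction in prevalence, and the difference can be derived from the model already specified.
- A reader might also infer that the odds ratio is all that will be reported. That goes too far, because a crude comparison of prevalence is planned. What is lacking is an estimate and interval that respect the clustering.
- The word difference, as a definition of the outcome, occurs only in the Abstract; Study Outcomes and Sample Size speak of prevalence at 12 months. This is correct, but the sample size is itself built on the difference, so the mismatch does not rest on the Abstract alone.
- Baseline oral health status is not defined as baseline caries and could mean plaque or gingival indices, and robust standard errors are allowed in place of a multilevel model. Hence the size of the shift from adjustment is open. One could invent a rate of new caries and set an odds ratio among initially caries-free students against a prevalence ratio among all students. That contrast would mix two populations, and existing caries diluting the outcome would drive much of it, so it is not relied on here.
- A post-estimation summary is often left to an analysis plan. That would answer a silence, but the article does state the effect measure, and it is on a different scale from the stated outcome.

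**Conclusion.** The point holds as a mismatch of moderate weight between the estimand and the reported measure. The plan names a prevalence difference and is sized on one, then commits to an adjusted odds ratio. Its only comparison on the prevalence scale ignores clustering. At the planning rates the gap is 0.44 for the odds ratio against 0.67 for the prevalence ratio and -20 points for the difference, which is plain arithmetic on the plan's own figures. That covariate adjustment moves the conditional odds ratio further from 1 is certain in direction for a covariate that predicts the outcome. Its amount rests on assumptions that the documents do not supply. The hypothesis test, the sample size and the data to be collected are not called into question.

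**What to change.** In Statistical Analysis, replace the sentence on effect estimates, for the binary primary outcome, with wording along these lines:

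*The primary effect estimate is the covariate-standardised (marginal) difference between arms in the proportion of students with caries at 12 months. It is obtained from the fitted primary model and reported with a 95% confidence interval that accounts for clustering, is suited to 12 schools and is combined across imputations. The standardised prevalence ratio and the adjusted odds ratio are supporting measures.*

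State the difference in Study Outcomes as well, so that it agrees with the Abstract.

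The cost is a modest post-estimation step in Stata, which the plan already names. Three details need settling: averaging over the school effect if the multilevel form is used, an interval that does not lean on large-sample theory with 7 and 5 schools, and what to do if nearly all students with caries at baseline still count as affected at 12 months, which can make a baseline-caries term predict the outcome almost perfectly. The headline number will look less striking than an odds ratio. No extra students, visits or data are needed, and the Results section says that analysis has yet to begin, so the change can still be prespecified.

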### Ethical Considerations

This study has been approved by the institutional review board of Sun Yat-sen University (approval 2025‐065) and will be conducted in accordance with the Declaration of Helsinki and relevant national ethical guidelines. Prior to participation, detailed information about the study objectives, procedures, potential risks, and benefits will be provided to all participants and their legal guardians. Informed consent will be obtained from the guardians of participating students younger than 18 years. For students aged 18 years or older, informed consent will be obtained from either the participant or a legal guardian with participant assent [28,29] (Multimedia Appendix 1).

Although FV is considered safe and adverse events are uncommon, all potential adverse reactions will be monitored and recorded [30]. Any adverse reactions will be managed promptly, with medical referral and ethics reporting as required. Participation in the study is voluntary, and individuals may withdraw at any time without penalty. All personal data will be anonymized and stored securely in password-protected systems accessible only to authorized research personnel. Only deidentified data will be used for analysis and reporting to ensure confidentiality.

## Results

This trial was funded by the Department of Education of Guangdong Province (grant YCKJ-2025‐30). Participant recruitment and school selection are expected to be completed by June 2025. Baseline data, including oral health examinations and questionnaires, were collected during the spring semester of 2025. Following baseline assessment, the intervention group received the first professional application of FV and tailored oral health education materials for parents and teachers. A second round of FV application will be delivered 6 months after the first intervention. The control group will continue with standard annual dental examinations without fluoride application. An overview of the study is shown in Figure 2. Data collection is scheduled to conclude in June 2026. Data analysis will begin after the completion of data collection. At the time of protocol preparation, school selection (n=12) was finalized, with 5 (41.7%) control schools and 7 (58.3%) intervention schools enrolled across 3 representative cities, and more than 1100 students had been recruited. Descriptive and analytic results are expected to be published in 2027.

## Discussion

### Hypothesized Findings

Biannual FV application, integrated with tailored oral health education for parents and teachers, is anticipated to be an effective intervention for caries control, significantly reducing the prevalence of dental caries among students in special education schools in Guangdong Province. We anticipate a significantly lower incidence of new caries and a higher rate of oral hygiene improvement—as measured by plaque and gingival indices—in the intervention group. Furthermore, the intervention is expected to significantly improve parental and teacher health literacy and oral health–related KAP scores. This study integrates professional clinical prevention with school-based education, aiming to generate critical evidence to inform national oral health strategies and policies for children with disabilities in China.

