To date, few randomized trials have evaluated FV as a standalone intervention in students attending special education schools, especially in low- and middle-income countries [3,11]. Existing research often combines FV with other interventions, targets only certain subtypes of disabilities (eg, intellectual disability), or lacks sufficient sample sizes and follow-up to assess effectiveness under real-world conditions [11]. In China, there is currently no trial evaluating the effect of FV in special education settings, nor any that incorporate systematic delivery through existing school health infrastructure.

This study addresses this critical evidence gap by evaluating a school-based FV intervention in special education schools in Guangdong Province, China, using a stratified cluster randomized controlled trial (RCT) design. The trial compares the effect of biannual FV applications, administered by trained professionals and accompanied by tailored oral health education for parents and teachers, with that of standard care alone. By assessing the impact of FV in a high-risk, underserved population, this study seeks to generate policy-relevant evidence to inform national oral health strategies for children with disabilities.

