### Intervention and Control

The intervention group will receive 2 professionally administered FV applications. Applications will occur at baseline (month 0) and at 6 months, using Duraphat (Colgate-Palmolive Company) varnish, which contains 5% sodium fluoride by weight, equivalent to 22,600 parts per million fluoride ions [16,17]. The varnish will be applied to all erupted tooth surfaces by trained dental professionals under standard infection control procedures, including hand hygiene, appropriate personal protective equipment, and the use of single-use disposable materials to prevent cross-contamination, in accordance with Centers for Disease Control and Prevention guidelines for portable dental care [18]. A brief oral examination will be conducted prior to each session to confirm eligibility for varnish application. Prior to application, the teeth will be cleaned with sterile gauze and isolated with cotton rolls for moisture control [19]. The tooth surfaces will then be dried with gauze, followed by the application of 0.40 mL of 5% sodium fluoride varnish [20]. Concurrently, oral health education will be provided to parents and teachers of students. These educational sessions will be delivered during the school visits in which varnish applications occur. Content will include basic oral hygiene practices, the importance of fluoride in caries prevention, dietary advice, and strategies for supporting children with disabilities in maintaining oral health.

The control group will receive standard care, consisting of annual oral health examinations and oral health education. These educational components will be delivered during routine school visits using the same materials and format as in the intervention group, ensuring comparability of educational exposure between groups. However, no FV will be applied in control schools during the study period. The overview of the study is shown in Figure 2.

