Baseline assessments will be conducted prior to intervention implementation, with follow-up occurring 12 months later. Oral examinations will be performed on-site in schools, with each child examined in a standardized manner. KAP questionnaires will be administered to parents and teachers at both baseline and the end of follow-up. All data will be collected using the Wenjuan Star platform (Shanghai Zhongyan Network Technology Co Ltd) or through paper-based questionnaires with double data entry, depending on the logistical feasibility at each study site. Data from paper questionnaires will be manually entered into the electronic system by trained students at the university. Details of the information collected are shown in Table 1. Monitors appointed by the trial sponsor will oversee trial implementation to ensure protocol compliance and data accuracy (Multimedia Appendix 1).

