### Conclusions

By using a stratified cluster randomized design, the study will provide evidence on the effectiveness of integrating professional FV applications into the special education school environment. If the hypothesized reduction in caries and improvement in health literacy is confirmed, this model could serve as a blueprint for national health authorities to implement scalable, cost-effective oral health programs.

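### Both arms are to receive the same education, so the randomised comparison cannot support the expected gain in parent and teacher health literacy and KAP

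*Protocol article*

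**What the plan says.** All references are to the protocol article.

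- **Control education (Intervention and Control).** Control schools get annual examinations and oral health education, delivered "using the same materials and format as in the intervention group, ensuring comparability of educational exposure between groups". The one element withheld is varnish: "However, no FV will be applied in control schools during the study period".
- **Abstract, Methods.** This agrees: "The control group will receive standard annual examinations and comparable oral health education".
- **Timing of intervention education (Intervention and Control).** "These educational sessions will be delivered during the school visits in which varnish applications occur", that is, at months 0 and 6. Control education takes place at routine school visits, whose number is not given.
- **Hypothesized Findings.** "the intervention is expected to significantly improve parental and teacher health literacy", and KAP scores as well.
- **Conclusions.** "If the hypothesized reduction in caries and improvement in health literacy is confirmed", the model is put forward as a possible blueprint for national authorities.
- **Results (main text).** Tailored education material is mentioned for the intervention arm at the first varnish round. The sentence on the control arm mentions annual examinations and the absence of fluoride, and is silent on education.
- **Statistical Analysis.** Between-group tests, mixed-effects models and within-group paired comparisons of baseline with 12 months are all planned.
- **Study Outcomes.** KAP change is a secondary outcome in students, parents and teachers, but "KAP questionnaires will be administered to parents and teachers at both baseline and the end of follow-up". Data Collection also names only parents and teachers as respondents.

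**The concern.** A randomised comparison estimates the effect of what differs between the arms. As Intervention and Control describes them, the arms differ in varnish and not in education. The hypothesis on literacy and KAP credits the intervention with an effect that only education would plausibly produce, and both arms receive education.

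Two things are at stake. First, both arms can be expected to improve on KAP after being taught, and the planned within-group paired tests could return a small P value in the intervention arm. Read alongside the Conclusions, that could be taken as the confirmation on which the policy recommendation depends, although it has no control. Second, if education is in fact heavier in the intervention arm, as the Results wording allows, a KAP difference could be real. The caries difference would then no longer be attributable to varnish alone.

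**Working it through.** **1. What differs between the arms, as described in Intervention and Control**

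| Component | Intervention | Control |
|---|---|---|
| Varnish | months 0 and 6 | none |
| Education materials and format | as described | the same |
| Education occasions | the varnish visits | routine visits, number not stated |

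**2. What each planned analysis estimates for KAP.** Let T be the change that would occur anyway, E the effect of education, and V any effect of varnish on KAP.

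- Intervention arm, within-arm change: T + E + V
- Control arm, within-arm change: T + E
- Between-arm difference: (T + E + V) − (T + E) = V

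A paired test in the intervention arm responds to T and E even when V = 0. The between-arm comparison removes both and leaves V, for which the article offers no mechanism on parent or teacher knowledge.

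If education differs (E₁ in the intervention arm, E₀ in the control arm), the between-arm KAP difference becomes (E₁ − E₀) + V. The caries difference by the same reasoning becomes the varnish effect plus the effect of the additional education.

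**3. The plan's own figures.** There is no sample size for KAP. The one for caries reproduces: (1.96 + 1.28)² × (0.24 + 0.24) / 0.20² = 125.97, so 126 per arm. The design effect is 1 + 149 × 0.02 = 3.98, and 126 × 3.98 = 501.5, given as 501. Then 501 / 0.90 = 556.7, so 557 per arm. This point changes none of these.

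**4. How a between-arm KAP test would behave (illustration).** The article gives no KAP effect size, standard deviation, intracluster correlation or number of respondents. Assume 501 respondents per arm and the caries design effect of 3.98. For a standardised difference d:

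- SE = √(2 × 3.98 / 501) = 0.126
- Power = Φ(d/SE − 1.96) + Φ(−d/SE − 1.96)

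| True d | Probability of P<.05 |
|---|---|
| 0 | 5% |
| 0.05 | 7% |
| 0.1 | 12% |
| 0.2 | 35% |
| 0.3 | 66% |

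A significant KAP benefit is therefore not the expected result if education is equal. The table also shows that a non-significant KAP difference would not prove that education was equal, so a record of sessions delivered is needed as well.

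**5. Student KAP.** Study Outcomes names students among those whose KAP is assessed, yet the named respondents are parents and teachers. Table 1 does record the child's brushing, toothpaste use, oral hygiene methods and diet, so some student practices are captured. No respondent is stated for student knowledge and attitudes.

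**The case against.** The sentence in Hypothesized Findings is an expectation in a discussion section and names no comparator, so it could be read as a within-group forecast. That reading does not rescue it. The sentence before it compares the arms, the improvement is credited to the intervention, and the Conclusions build on it.

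Several stronger readings are tempting, and the objections to them stand:

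- *The paired test is the only analysis that could show KAP change.* It is not. The planned between-group tests and mixed-effects linear models can cover KAP scores. That the paired result would be misused is a risk, not a stated intention.
- *The between-arm KAP effect is exactly zero.* This is not shown. KAP includes attitudes and practices, and the trial is open label, so families and teachers who know that varnish was given might respond to that. What can be said is that no route to knowledge is given and no large difference is to be expected.
- *Intervention schools get two education sessions and control schools one.* The article does not say so. The word annual is attached to the examinations, control visits are plural and uncounted, and a session count may sit in the full protocol.
- *The Introduction contradicts equal education.* It compares varnish "accompanied by tailored oral health education for parents and teachers, with that of standard care alone", but Intervention and Control defines standard care as including education, so the two fit. The Results wording is harder to square, although it does not say that control schools get no education.
- *Student KAP has no data.* This goes too far, given the practice items in Table 1.

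It is also fair to say that dropping the between-arm KAP comparison, or deleting students from the outcome, after baseline collection would be an unnecessary change. That comparison is valid and useful.

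**Conclusion.** The concern holds in a limited form. Taking the statement of comparable education at its word, the trial tests varnish added to education. It cannot support a claim that the intervention improves parent or teacher health literacy or KAP through education, and the blueprint conclusion should not depend on one. A pre-post gain would be expected in both arms and would not be a randomised effect.

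If equal education leaves no true KAP difference, the chance of a significant between-arm result is 5%. The other probabilities in the table rest on assumed respondent numbers and a borrowed design effect. The documents do not establish that education is unequal. They contain wording in the Results that must be reconciled with Intervention and Control, and if exposure does differ, the caries result mixes varnish with education. The primary outcome, sample size and primary model are otherwise untouched.

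**What to change.** 1. State the randomised contrast once, as varnish added to equal education, and align the Results wording with it.
2. In Hypothesized Findings, remove improvement in literacy and KAP as an expected effect of the intervention. In the Conclusions, remove it as a condition for the blueprint.
3. Keep KAP as a secondary outcome, judged only by the cluster-adjusted between-arm comparison and reported with its confidence interval. State that no large difference is expected and that the comparison serves as a check on equal education. Report within-arm change descriptively, with no efficacy claim.
4. Record the education sessions delivered in each of the 12 schools. If they differ between arms, word the caries conclusion as varnish plus additional education.
5. Reconcile the student KAP outcome with the named respondents, for example by stating that student practices are caregiver-reported.

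The cost is a few sentences and a simple log. Follow-up was still under way and analysis had not begun when the article was written. The sponsor gives up an education-effect claim that the design cannot support.
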